## Abstract

**Background:**

Shared decision making contributes to high quality healthcare by promoting a patient-centered approach. Patient involvement in selecting the components of a diabetes medication program that best match the patient’s values and preferences may also enhance medication adherence and improve outcomes. Decision aids are tools designed to involve patients in shared decision making, but their adoption in practice has been limited. In this study, we propose to obtain a preliminary estimate of the impact of patient decision aids vs. usual care on measures of patient involvement in decision making, diabetes care processes, medication adherence, glycemic and cardiovascular risk factor control, and resource utilization. In addition, we propose to identify, describe, and explain factors that promote or inhibit the routine embedding of decision aids in practice.

**Methods/Design:**

We will be conducting a mixed-methods study comprised of a cluster-randomized, practical, multicentered trial enrolling clinicians and their patients (n = 240) with type 2 diabetes from rural and suburban primary care practices (n = 8), with an embedded qualitative study to examine factors that influence the incorporation of decision aids into routine practice. The intervention will consist of the use of a decision aid (*Statin Choice* and *Aspirin Choice,* or *Diabetes Medication Choice*) during the clinical encounter. The qualitative study will include analysis of video recordings of clinical encounters and in-depth, semi-structured interviews with participating patients, clinicians, and clinic support staff, in both trial arms.

**Discussion:**

Upon completion of this trial, we will have new knowledge about the effectiveness of diabetes decision aids in these practices. We will also better understand the factors that promote or inhibit the successful implementation and normalization of medication choice decision aids in the care of chronic patients in primary care practices.

**Trial registration:**

NCT00388050

## Background

Type 2 diabetes mellitus is a metabolic derangement of epidemic impact that lowers the quality and duration of life for millions [1]. The public health impact of this epidemic is best understood when considering that diabetes is associated with an increased risk of premature death (mostly from cardiovascular causes), cardiovascular disease, blindness, renal failure, chronic neuropathic pain, and limb amputations. Successful management of type 2 diabetes requires preventive care and incorporation of healthy nutritional and activity habits. Pharmacologic therapy to achieve metabolic control and favorably impact risk factors associated with diabetes-related complications is almost always necessary. Several medications to control hyperglycemia, hypertension, and dyslipidemia have become available in the last decades. Patients who experience the use of these medicines, often in combination, and their costs and side effects often report their burden to exceed the perceived burden of diabetes complications [2,3].

A patient-centered approach to care that promotes patient involvement in selecting the intensity and components of a complex diabetes medication program to better match patient values and preferences contributes to high quality care and may enhance medication adherence [4]. Decision aids, tools to help involve patients in decision making by clearly and accessibly presenting the available options and their relative advantages and disadvantages, may facilitate patient-centered care [5]. In close collaboration with a multidisciplinary team of patients, clinicians, and designers, we have developed decision aids targeting glycemic and cardiovascular risk factor control through medication therapy (*Diabetes Medication Choice, Statin Choice*) [6,7]. These tools have been shown to improve patient knowledge, involvement in the decision making process, and satisfaction with healthcare [6,8]. In addition, ninety percent of the clinicians considered the decision aids helpful and would use these decision aids in their practice [8].

Despite their efficacy [5], the adoption of decision aids in practice has been dismal for reasons that remain unclear. Furthermore, limited evidence supports our understanding of how decision aids become routinely implemented, embedded, and sustained in practice—that is, how they become normalized. Current approaches to understanding the implementation of decision aids in practice have included analyses of the barriers to using decision aids [9], and problems of individual behavioral change [10] or organizational diffusion. To our knowledge, there is no practice-based research focused on how to normalize these decision aids in the routine of busy clinical practices and on evaluating the effectiveness of diabetes decision aids on patient, clinician, and practice outcomes. Thus, there is urgent need to conduct patient-centered translational practice-based research in diabetes care.

To pursue this effort we propose to 1) evaluate, in a cluster-randomized practical trial enrolling primary care practices and their patients with type 2 diabetes, the impact of patient decision aids vs. usual care on measures of patient involvement in decision making, diabetes care processes, medication adherence, glycemic and cardiovascular risk factor control, and resource utilization; and 2) identify, describe, and explain, using a theory-driven qualitative research approach, factors that promote or inhibit the routine embedding of decision aids in the rural and suburban practices participating in the randomized trial.

## Methods

### Study design

We will be conducting a mixed-methods study comprised of a cluster-randomized, practical, multi-centered trial enrolling primary care practices with a qualitative study embedded to examine how the practices will be incorporating the decision aids into their clinical routines (Figure 1). The Mayo Clinic and Olmsted Medical Center Institutional Review Boards (IRB) have approved the study procedures described herein.

**Figure 1 F1:**
[figure not shown]
Study design.

### Setting

We will recruit clinicians and their patients with type 2 diabetes receiving routine diabetes care from participating primary care practices of Olmsted Medical Center across rural and suburban communities in Southeastern Minnesota, USA.

### Study participants and eligibility criteria

***Clinical practices.*** Eligible practices are those that have prioritized chronic disease care as an area for quality improvement and have served at least 50 patients with type 2 diabetes in the 12 months prior to the eligibility assessment. ***Primary care clinicians.*** We will recruit clinicians, defined as professionals with patient healthcare responsibilities (i.e., physicians, nurse practitioners, physician assistants), from participating practices if they are providing care to adults with type 2 diabetes. ***Patients.*** We will consider eligible adult patients (≥18 years) with type 2 diabetes if they recognize the participating clinician as their main diabetes care provider, have no major barriers to provide written informed consent (e.g., severe hearing impairment, dementia), can communicate in English, and declare being available for a six-month follow-up. Furthermore, these patients should need to start, intensify, or modify their antihyperglycemic treatment. Additional criteria will be used to identify eligibility according to designated study arms (Figure 2).

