### Allocation procedures

Randomization will be by practice. The study will compare the use of the decision aids within the clinical encounter versus usual care. We will identify pairs of practices that are most similar in size (i.e., number of clinicians seeing adult patients with type 2 diabetes) and randomize within each pair to use either the 1) the *Statin Choice* and the *Aspirin Choice*, or 2) the *Diabetes Medication Choice* decision aid. Each practice will also serve as the usual care arm for the other intervention arm (Figure 2). This approach will seek to ensure similar representation of ‘easy’ and ‘difficult’ practices in both decision aid groups and eliminate the need for any site to simply serve as a usual care arm. A study statistician will perform the randomization centrally after the practices have been enrolled, ensuring concealment of allocation of the paired practices. Practices, clinicians, patients, and investigators will not be masked to the intervention. However, patients providing outcomes will remain masked to their practice status, as consent documents will keep patients unaware of the study’s main hypotheses. Furthermore, we will centrally follow patients and ensure that patient surveys and pharmacy follow-up are completed according to the intention-to-treat principle.

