#### Training of clinicians

A study team member will conduct a demonstration showing how to use the decision aid at the time of the initial in-person discussion with clinics. The focal points of the demonstration will be that decision aids serve as guides for conversation rather than scripted discussions; that clinicians have flexibility in the manner in which they use the decision aid, including how and when they use them during the visit; and that they may elect not to use the tools with certain enrolled patients, per their own judgment. Brief video clips and storyboards that demonstrate the basic use of decision aids are publicly available at http://kercards.e-bm.info for clinicians to review at their convenience. A study team member will remain available to do one-on-one demonstrations after the initial group demonstration if needed.

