### Usual care

For patients in the usual care arm, clinicians will manage the discussion about medication regimen as usual, without using decision aids.

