##### Sample size

A total of 8 practices will be randomized to 1) the Diabetes Medication Choice decision aid plus statin and aspirin usual care or 2) the Statin Choice and Aspirin Choice decision aids plus diabetes medication usual care. The Statin Choice cluster randomized trial evaluated decision quality comparing the decision aid to usual care. This study reported a 9.8 point difference in decision quality^3^ with the standard deviation of 16.9 and 14.1 for the usual care and decision aid groups, respectively. Making the following assumptions: 1) variances are as reported in this study; 2) we seek to detect a difference of 9.8 points or greater in decision quality between two groups at significance level of 0.05, with a two-sided *t*-test; 3) a modest correlation of outcomes across these clinicians and practices (which is a conservative assumption) represented by an intracluster correlation coefficient (ICC = between cluster variance/total variance) of 0.05; 4) a variance inflation or design effect factor [1+ (n − 1) · ICC], where n is the number of patients per cluster [31]; and 5) an approximated 20% attrition rate, we will have 80% power if we are able to recruit 30 patients per clinic for a total recruitment target of 240 patients. Assuming a similar ICC and attrition rate for other outcomes, this sample size will have 99% power to detect a 1 SD difference in any continuous measure (e.g., approximately a 2-point difference in a 10-question knowledge scale), and 80% power to detect a 30% difference in 6-month adherence rates assuming a control adherence rate of 50%. Actual power will be likely greater because we will adjust for baseline values and characteristics and because of our conservative assumptions.

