##### Analysis

We will have a summary of the cluster level and patient level characteristics within each trial arm, providing counts and frequencies for categorical variables and means with ranges for continuous variables. Because of the uncertainty as to the ability of a cluster trial to create uniform prognostic groups, we will test the null hypothesis of no difference between arms in baseline cluster level characteristics using the weighted paired *t*-test [32]. This test can account for the small number of clusters and an unequal number of patients within each cluster.

To account for the modified study design (e.g., each arm being both intervention and usual care), the study team assumes similar adherence rates within statin medications and diabetes medications along with similar knowledge, decisional conflict, and satisfaction rates for patients discussing either medication for those within the usual care group. For the decision aids (Statin, Aspirin and Diabetes Medication) the study team assumes the same impact on all of these outcomes for all decision aids. With these assumptions, all patients that use a decision aid during the encounter of interest will be grouped in the decision aid arm and those that do not will be grouped under the usual care arm. To account for differences that may exist between the diabetes, statin, and aspirin patients, all models will be adjusted by group. Interaction between arm and group will be tested for significance, recognizing that the study will be underpowered to test for this interaction.

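### The entry rule asks every patient to need an antihyperglycemic change, which conflicts with the statin/aspirin usual-care controls and separate topic groups the design relies on

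*Protocol article*

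**What the plan says.** All places are in the Protocol article.

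- **Study participants and eligibility criteria.** After the general patient criteria comes "Furthermore, these patients should need to start, intensify, or modify their antihyperglycemic treatment". The next sentence reads "Additional criteria will be used to identify eligibility according to designated study arms (Figure 2". Figure 2 is not shown.
- **Allocation procedures.** "Each practice will also serve as the usual care arm for the other intervention arm".
- **Usual care.** For these patients, "clinicians will manage the discussion about medication regimen as usual, without using decision aids".
- **Sample size (Aim 1).** "A total of 8 practices will be randomized to 1) the Diabetes Medication Choice decision aid plus statin and aspirin usual care", or to the reverse arrangement.
- **Training of clinicians.** Clinicians are told that "they may elect not to use the tools with certain enrolled patients, per their own judgment".
- **Analysis (Aim 1).** "all patients that use a decision aid during the encounter of interest will be grouped in the decision aid arm", and everyone else goes to usual care. The same section treats diabetes, statin and aspirin patients as groups to adjust for. It takes the HbA1c outcome only in those whose visit included a talk about diabetes drugs.

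**The concern.** The design has each practice deliver one aid and act as control for the other. For that to work, a practice using the diabetes aid must enrol some patients whose medication decision concerns a statin or aspirin and who are seen without an aid. The eligibility sentence admits only patients who also need a glucose-lowering change, so each such control is at the same time a candidate for the aid that practice is using.

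What is at stake is who can serve as a control. A patient who faces only a statin or aspirin decision is excluded as the text stands. A statin/aspirin control in a diabetes-aid practice stays a control only if the clinician leaves the aid unused. That makes control status there depend on a clinician's choice after randomization rather than on practice allocation.

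**Working it through.** **1. The planned figure.** The Sample size section gives a difference of 9.8, SDs of 16.9 and 14.1, two-sided alpha 0.05, ICC 0.05, 20% attrition and 30 patients per clinic in 8 clinics.

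- Pooled SD = sqrt((16.9² + 14.1²)/2) = 15.56.
- Unclustered n per arm = 2 x (1.960 + 0.842)² x 15.56² / 9.8², which rounds up to 40.
- Design effect = 1 + (30 − 1) x 0.05 = 2.45.
- Total = 2 x 40 x 2.45 / 0.80 = 245, against 240 stated.
- With 240 x 0.80 / 2 = 96 completers per arm, effective n is 96 / 2.45 = 39.2 and power is 0.796.

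The stated 240 patients and 80% power reproduce. This calculation uses two equal arms.

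**2. When equal arms arise.** Suppose a share p of patients in every practice is enrolled for the diabetes topic and the rest for statin/aspirin, and status follows topic and allocation. The aided arm is then 4 x 30 x p + 4 x 30 x (1 − p) = 120, whatever p is. The usual-care arm is the other 120. So the balance needs distinct topics, sorted in the same way in all practices.

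**3. The entry rule set against the other sections.**

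| Requirement elsewhere | Under the entry rule read literally |
|---|---|
| Statin/aspirin usual care in diabetes-aid practices (Allocation procedures, Sample size) | Each such patient also needs a glucose-lowering change and is a candidate for the diabetes aid |
| Usual care without an aid (Usual care) | Holds only where the diabetes aid is not used |
| Separate diabetes, statin and aspirin groups (Analysis) | Every patient meets the diabetes criterion |
| HbA1c only in a subset with a diabetes medication discussion (Analysis) | Hard to explain if every patient needs a diabetes drug change |

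An additional criterion can narrow a general one but cannot lift it. If Figure 2 admits statin/aspirin patients with no glucose-lowering change, it contradicts the eligibility text. If it does not, the mismatches in the table remain. The conflict stands either way.

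**4. Following the arm rule.** The Analysis section gives each patient one arm according to aid use in the encounter. A statin/aspirin control in a diabetes-aid practice who is shown the diabetes aid therefore moves to the aided arm. The controls left in that practice are those for whom the aid was not used.

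**5. Sensitivity, as an illustration only.** Assume every patient in the four diabetes-aid practices is aided, and a share s in the other four. The document gives neither figure. With 192 completers, usual care has 96(1 − s) and the aided arm 96(1 + s). Then SE² = 2.45 x [16.9²/(96(1 − s)) + 14.1²/(96(1 + s))], and power = Φ(9.8/SE − 1.96).

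| s | Usual care / aided | Power |
|---|---|---|
| 0 | 96 / 96 | 0.80 |
| 0.25 | 72 / 120 | 0.75 |
| 0.5 | 48 / 144 | 0.64 |
| 0.75 | 24 / 168 | 0.41 |

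Applying one design effect to arms that mix within practices is a simplification. The table shows what depends on the point and is no forecast.

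**The case against.** The strongest reply is that this is a misplaced sentence and not a broken design. Figure 2 is where patients are assigned by arm, and it is not shown. The Analysis section speaks of distinct patient groups and of a subset with a diabetes medication discussion, so the authors evidently expected some patients without one. That reading is plausible. It accounts for the conflict but does not remove it, because a site that applies the written criterion still turns away the patients the other sections need.

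A reader might go further and infer that none of the 120 patients in the diabetes-aid practices could be a statin/aspirin control, or that the control arm for that topic does not exist. The documents do not support this. Needing a change is not the same as discussing it at the index visit, clinicians may leave the aid unused, and Figure 2 is unseen. Non-use does leave some unaided patients, although they are selected by the clinician.

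A reader might also infer that one patient is counted as both aided and unaided. The Analysis section rules that out, since each patient has one arm. Nor is it a defect that the article does not say which decision the Decisional Conflict Scale items address. An article may leave that to the full protocol and the questionnaires.

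**Conclusion.** The conflict is real and rests on the visible text. The eligibility section applies the antihyperglycemic criterion to everyone, while Allocation procedures, Usual care, Sample size and Analysis presuppose patients it would exclude or expose to the other aid. Read literally, it affects the composition of the control group in the four diabetes-aid practices, which hold 120 of the 240 planned patients. How many controls would be lost, and how much power or bias that means, cannot be determined from the article; the power range above rests wholly on assumed aid use. The stated sample size is arithmetically sound. The conclusion assumes only that additional criteria do not override the general one. It holds whether the sentence is a slip or intended, and it should be settled because it decides who is enrolled and who can be a control.

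**What to change.** Reconcile the eligibility section with Figure 2, Allocation procedures, Sample size and Analysis in two steps.

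1. State that the antihyperglycemic criterion applies to patients enrolled for the diabetes-medication topic.
2. Assign each patient one index topic from the record before the visit, by the same rule in all practices, and say how a patient eligible for both topics is classified. Let aided or usual-care status follow from index topic and practice allocation, and align the grouping sentence in the Analysis section with this.

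The cost is a wording change and a small amount of pre-visit classification work. Some patients eligible for both topics may still be shown the aid for their non-index topic. The planned video recordings allow this to be noted, and it would no longer change the patient's arm. There is no need to exclude statin/aspirin patients who also have an antihyperglycemic change planned. That would narrow a practical trial and could slow recruitment toward 30 per clinic.

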**Figure 2 F2:**
[figure not shown]
Eligibility criteria and assignment by arms.

### Participant recruitment

We will send an introductory letter providing an overview of the study and inquiring about potential interest to eligible practices. Study team members will then personally visit interested clinics to discuss the study in more detail with clinic leaders. We will identify a lead clinician (“clinical champion”) to become the contact person for each practice for the duration of the study and seek participation of clinicians during this first meeting when the study is discussed. Potentially eligible patients will be identified through the diabetes registry, and we will note their upcoming appointments with participating clinicians. A study team member will contact these patients in advance to seek their participation in the study. Trained study personnel will obtain written informed consent to participate in the study from both clinicians and patients prior to their clinical encounter.

### Allocation procedures

Randomization will be by practice. The study will compare the use of the decision aids within the clinical encounter versus usual care. We will identify pairs of practices that are most similar in size (i.e., number of clinicians seeing adult patients with type 2 diabetes) and randomize within each pair to use either the 1) the *Statin Choice* and the *Aspirin Choice*, or 2) the *Diabetes Medication Choice* decision aid. Each practice will also serve as the usual care arm for the other intervention arm (Figure 2). This approach will seek to ensure similar representation of ‘easy’ and ‘difficult’ practices in both decision aid groups and eliminate the need for any site to simply serve as a usual care arm. A study statistician will perform the randomization centrally after the practices have been enrolled, ensuring concealment of allocation of the paired practices. Practices, clinicians, patients, and investigators will not be masked to the intervention. However, patients providing outcomes will remain masked to their practice status, as consent documents will keep patients unaware of the study’s main hypotheses. Furthermore, we will centrally follow patients and ensure that patient surveys and pharmacy follow-up are completed according to the intention-to-treat principle.

